### Statistical methods

Descriptive and frequency statistics will be used to assess qualitative variables. Normality of quantitative variables (i.e. pixel area) will be examined using histograms and the Kolmogorov-Smirnov test protected by the Bonferroni correction. To assess differences in quantitative measurements between study groups, parametric and non-parametric tests will be performed as appropriate, respectively. Correlation between clinical data and OCTA derived measurements will be analyzed using a multivariate regression model to assess the effects of clinical characteristics on these values. Visual acuity measured in Snellen notation was converted to logMAR (logarithm of the minimum angle of resolution) equivalents for the purposes of statistical analysis. VA values recorded as counting fingers (CF), hand movements (HM), and perception of light (PL) were converted to 2.1, 2.4, and 2.7 LogMAR, respectively. A *p* value of less than 0.05 will be considered statistically significant. All statistical analysis will be performed using IBM SPSS Statistics software version 21.0 (IBM Corp., Armonk, NY, USA).

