### Sample size

Given that no normative databases are available for vessel density in normal eyes the project was designed in an exploratory basis. In our hospital, an estimate number of 2000 type I DM patients are seen in a yearly basis, which will be offered to enter the study voluntarily. All patients willing to participate during the study period will be included. We anticipate an estimated opt-out rate of 50%, with a final estimated sample size of 1000 patients.

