### Study groups

Type I DM patients with and without existing diabetic retinopathy (DR) will be included in the study. Both groups will be classified by duration of diabetic disease (defined as date of type I DM diagnosis), in 3 main groups: A. ≤5 years from diagnosis, B. > 5 - < 15 years from diagnosis, and C. ≥15 years from diagnosis. Subgroup analysis will include also treatment type, glycemic control (glycaemia and HbA1c), body mass index, lipid profile and kidney function tests. A cohort of 100 normal eyes (controls) from a pool of healthy volunteers with clear media and without retinal disease will undergo retinal imaging with OCTA for comparison with type 1 DM cases images.

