**Fig. 2 Fig2:**
[figure not shown]
Examples of OCTA image datasets collected for each individual patient and eye included in the study (3 × 3, 6 × 6 and 8 × 8 mm scan sizes, Angioplex, Cirrus HD-OCT, Carl Zeiss Meditec, Dublin, CA, USA). Similar images were obtained with a different swept source device for each study eye (3 × 3, 6 × 6 and 9 × 9 mm, Triton Deep Range Imaging -DRI- OCT, Topcon Corp, Topcon, Japan)

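### The main comparisons are between eyes, but the stated tests and regression make no provision for two eyes of one person; if both eyes enter, standard errors for duration and systemic factors are too small

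*Protocol article*

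**What the plan says.** The units differ between sections of the protocol article:

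- Sample size counts people, "with a final estimated sample size of 1000 patients".
- Study groups counts eyes for the comparison cohort, "A cohort of 100 normal eyes (controls) from a pool of healthy volunteers". The Triton section repeats this. Neither gives the number of volunteers.
- The Fig. 2 legend describes the imaging as "Examples of OCTA image datasets collected for each individual patient and eye included in the study" and adds "Similar images were obtained with a different swept source device for each study eye".
- Main outcome measures lists four comparisons, all framed in eyes: controls against diabetic eyes, eyes without against eyes with retinopathy, and duration bands within each of those two groups.
- Study groups describes retinopathy status as an attribute of patients and divides both patient groups into three duration bands.

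Statistical methods gives two analyses. For groups: "To assess differences in quantitative measurements between study groups, parametric and non-parametric tests will be performed as appropriate, respectively". For clinical factors: "Correlation between clinical data and OCTA derived measurements will be analyzed using a multivariate regression model". A p "value of less than 0.05 will be considered statistically significant". The article has no rule for choosing one eye or averaging two, and no paired, clustered or mixed analysis.

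**The concern.** Fellow eyes share a person's age, glycaemic history, disease duration and vascular anatomy, so their vessel density and avascular-zone measurements can be expected to correlate. Standard parametric and rank tests, and ordinary regression, treat each row as a separate piece of evidence. If both eyes are entered as separate rows, the analysis counts more information than it has.

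This affects the central questions. Duration, HbA1c, glycaemia, body mass index, lipids, kidney function and treatment type take one value per person, so for them the second eye adds little. Recruiting more patients does not cure it, because the understatement is a fixed proportion of the standard error. The Discussion says that associations, if found, may lead to OCTA being included in screening, so false-positive associations would have consequences.

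The retinopathy comparison has a further difficulty. If status is assigned by eye, a patient with one affected eye falls in both groups; if by patient, in one. The article uses both units and does not reconcile them.

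**Working it through.** **Inputs**

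- Level 0.05 (Statistical methods). Sidedness is not stated; taken as two-sided, critical value 1.96.
- Patients: 2000 × (1 − 0.50) = 1000, which reproduces the figure in Sample size. It is a count of people, hence 2000 eyes if both enter.
- Controls: 100 eyes (Study groups), so between 50 and 100 persons.
- Inter-eye correlation rho: not in the document. Assumed 0.2 to 0.9. The relevant value is the correlation left within groups, or after covariates in the regression.
- Eyes analysed per person: not stated. Two is assumed first, then varied.

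**Step 1: both eyes of every person, both in the same group.** This is the situation for duration and the systemic factors. The variance of a group mean is (1 + rho) times what an independence analysis assumes, so

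true level = 2 × [1 − Phi(1.96 / sqrt(1 + rho))].

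| rho | SE too small by factor | true level | 2000 eyes are worth (2000/(1 + rho)) |
|---|---|---|---|
| 0.2 | 1.10 | 7.4% | 1667 |
| 0.3 | 1.14 | 8.6% | 1538 |
| 0.5 | 1.22 | 11.0% | 1333 |
| 0.7 | 1.30 | 13.3% | 1176 |
| 0.9 | 1.38 | 15.5% | 1053 |

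These levels are for a single contrast, such as two duration bands or one regression coefficient. An overall test across the three bands has 2 degrees of freedom and, in large samples, a level of 0.05^(1/(1 + rho)): 0.05^(1/1.5) = 13.6% at rho 0.5. The single-contrast figures are therefore not the worst case for that test.

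**Step 2: simulation check.** 300 against 400 persons, two eyes each, no true difference, 4000 runs. At rho 0.5, 0.7 and 0.9 the t-test rejects in 11.2%, 13.3% and 16.0% of runs and Mann-Whitney in 10.6%, 13.6% and 15.5%. Simulation error is about half a percentage point (sqrt(0.13 × 0.87 / 4000) = 0.005). A separate simulation of a t-test on patient means returned 5%.

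**Step 3: only some persons give two eyes.** With a share s giving two, the variance factor is 1 + 2·s·rho/(1 + s). For s = 0.5 it is 1.33 at rho 0.5 and 1.60 at rho 0.9, giving levels of 9.0% and 12.1%.

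**Step 4: controls against 2000 diabetic eyes.** The variance factor is [c/100 + (1 + rho)/2000] / [1/100 + 1/2000], where c = 1 if the control eyes come from 100 persons and c = 1 + rho if from 50.

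- 100 persons: at rho 0.5, (0.01 + 0.00075)/0.0105 = 1.024, level 5.3%; at rho 0.9, level 5.5%.
- 50 persons: 11.0% to 15.5%, and the 100 eyes are worth 100/1.9 = 53 to 100/1.5 = 67 independent eyes.

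**Step 5: retinopathy by eye, some patients affected in one eye only.** Assume 20% of 1000 patients are discordant and the rest split 30% both eyes affected, 70% neither: 240 both, 560 neither, 200 discordant, so n1 = 680 and n0 = 1320 eyes. The true variance is proportional to

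(680 + 480·rho)/680² + (1320 + 1120·rho)/1320² − 400·rho/(680 × 1320),

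against 1/680 + 1/1320 under independence. At rho 0.5 the ratio is 0.002846/0.002228 = 1.28, level 8.3%; at rho 0.9 the level is 10.9%. With 30% discordant the levels are 7.1% and 8.7%.

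**The case against.** The best defence is that the article nowhere says that both eyes are analysed. The figure legend's wording also fits one designated study eye per person, the sample is stated in patients and never as 2000 eyes, and images could be taken of both eyes while one is analysed. With one eye per person there is no inflation. No test is named either, and an eye-selection rule or clustering term could sit in the full protocol or an analysis plan that is not shown. The study is declared exploratory, makes no power claim, and the problem concerns precision rather than bias in group means.

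Most of this stands as a limit on the claim. It does not remove the point: the article itself fixes the eye as the unit of comparison, counts its two cohorts in different units, and describes the analysis in terms that, followed as written with both eyes entered, give wrong standard errors.

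A reader might infer several stronger statements that the document does not support:

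- That the plan's 5% level is 11% to 16%. That needs an assumed rho of 0.5 to 0.9, two eyes from everyone, and both eyes in the same group.
- That all four main comparisons are affected alike. Steps 4 and 5 show that they need not be.
- That the controls are only 50 people. That is one end of a 50-to-100 range.
- That the retinopathy contrast errs in the opposite direction because of discordant patients. Discordance reduces the inflation, but in every mix calculated (10% to 30% discordant) the level stays above 5%.
- That only two-group tests are planned. No test is named, and duration has three bands.

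**Conclusion.** The concern holds in conditional form. The unit of analysis is not consistently fixed, and the stated methods contain nothing for within-person correlation. If both eyes enter, which is the natural but not the only reading, the standard errors for duration and systemic factors are understated by 10% to 38% as a multiple of the reported value, and single contrasts run at about 7% to 16% instead of 5%. That range rests on rho between 0.2 and 0.9 and two eyes from every person. Controls against diabetic eyes could be almost unaffected (about 5.3% to 5.5%) if the controls are 100 people. Retinopathy against none would lie at about 8% to 11% with an assumed 20% of patients discordant. The group means themselves are not biased by this, and the data collected are sufficient to correct it.

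**What to change.** In Statistical methods, state that eye-level outcomes will be analysed with a linear mixed model with a random intercept per person, or with GEE clustered on person. Retinopathy status should enter as an eye-level covariate, and duration, HbA1c and the other systemic factors as person-level covariates. Alternatively, state that one eye per person is analysed and fix the selection rule before the images are measured. That is simpler but discards information: at rho 0.5, both eyes of 1000 patients are worth 1333 independent eyes against 1000.

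Reconcile Study groups with Main outcome measures by saying whether retinopathy is classified by eye or by patient. Give the control cohort in persons as well as eyes.

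The cost is wording and a different procedure in SPSS, the package already named, which offers both methods. No new data are needed. Intervals for person-level factors become wider and p-values less favourable.

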## Discussion

This study is directed to evaluate the potential role of OCTA as a useful tool to inform the status of the macular microvascular network in type 1 Diabetes Mellitus patients. Its prospective nature and collaborative design between endocrinologists and ophthalmologists may allow the recruitment of a large cohort of type 1 DM patients and controls to permit the study of potential relationships between the perifoveal vascular network parameters obtained with OCTA and systemic markers of the disease. The positive or negative results of this study will be communicated in scientific meetings and publications. If these relationships are identified OCTA may be included in the screening program of type 1 DM patients, as these changes may preceed the progression to more advanced stages of diabetic retinopathy (i.e. from non DR to mild DR stages), as well as reflect the status of the microvasculature in other parts of the body only accessible by invasive procedures, such as kidney or heart biopsies. The potential of this technology will be evaluated in this and future trials.

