**Discussion:**

This study is directed to investigate the relationship between the status of the perifoveal vascular network and systemic markers of the disease, and in particular to study whether these changes reflect those occurring elsewhere in the body affected by diabetic microvascular disease, as the kidneys or the brain. If these relationships were demonstrated, early detection of these microvascular changes by OCTA could lead to modifications in the pharmacological management of type 1 diabetic patients, as a way to reduce the risk of future complications in both the eye and other organs.

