## Methods

### Study design

Cross sectional, exploratory study in a cohort of type I DM patients seen in the Endocrinology service in a 36-month period from May 2017, with prospective collection of OCTA images and relevant clinical data. This study is registered in the Clinical Trials website (ClinicalTrials.gov, trial number NCT03422965). The Standard Protocol Items Recommendations for Interventional Trials (SPIRIT) 2013 checklist was addressed in the present paper (Additional file 1).

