### Interventions

#### Systemic data

Systemic status of the diabetic disease will be evaluated in routine clinical care examinations in the Diabetes Unit of the Endocrinology service, and clinical data collected will include: Demographics, date of diagnosis, duration of disease, treatment type, glycaemia, HbA1c levels, concomitant pathology (hypertension, etc.), body mass index, lipid profile (total cholesterol, triglycerides, HDL-cholesterol, LDL-cholesterol) and kidney function tests (urinary albumin excretion, estimated filtration glomerular rate).

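### The screening aim and outlook go beyond an analysis of group differences and regression at p<0.05, and the time-order and brain/heart remarks go beyond the design and the data listed

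*Protocol article*

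**What the plan says.** The last paragraph of the Background gives the aim as evaluating OCTA as a non-invasive screening tool for early perifoveal change in type 1 diabetes. The objectives that follow are to describe the capillary network across groups and to look for associations with demographic, metabolic and other risk factors.

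Main outcome measures lists vessel density, total avascular area and the foveal avascular zone. They are compared between controls and diabetic eyes, between eyes without and with retinopathy, and across duration bands. Statistical methods provides parametric or non-parametric tests for group differences and a multivariate regression of OCTA values on clinical characteristics. The only criterion given is that a p "value of less than 0.05 will be considered statistically significant".

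Study design calls this a "Cross sectional, exploratory study in a cohort of type I DM patients".

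The Discussion looks ahead to screening use on one condition: "If these relationships are identified OCTA may be included in the screening program of type 1 DM patients". The reason it offers for this prospect concerns order in time: "as these changes may preceed the progression to more advanced stages of diabetic retinopathy". It adds that they may also "reflect the status of the microvasculature in other parts of the body only accessible by invasive procedures, such as kidney or heart biopsies". The Discussion paragraph of the Abstract says the study is intended in particular "to study whether these changes reflect those occurring elsewhere in the body affected by diabetic microvascular disease, as the kidneys or the brain". For organs other than the eye, Systemic data lists "kidney function tests (urinary albumin excretion, estimated filtration glomerular rate"). It names no brain or heart measure; the nearest item is concomitant pathology, with hypertension as the example.

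**The concern.** A screening role depends on how well a measurement separates one person from another. A test of mean difference, or of a non-zero regression coefficient, answers a different question, and in a large sample the two answers can be far apart. If the prospect of screening hangs on relationships being identified, and the only criterion for identifying one is p<0.05, a very weak association could be cited in its favour.

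Two further statements outrun the plan. Order in time cannot be read from one examination per patient, and the planned duration bands contain different people. The Abstract also names the brain as something the study examines, while the data list has no variable for it.

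What is at stake is the interpretation of the results. The Abstract goes on to mention possible consequences for patients' treatment, so the evidence needed for such statements is best fixed before results are seen.

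**Working it through.** **Inputs from the protocol article**
- Patients: about 2000 seen per year and 50% opting out (Sample size).
- Controls: 100 normal eyes (Study groups).
- Significance level: 0.05 (Statistical methods), taken here as two-sided.

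**Assumed**, because the article does not give it: 20–40% of patients have retinopathy. A wider range of 10–50% is also shown.

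**Step 1. The plan's own figure.** 2000 × (1 − 0.50) = 1000 patients. This reproduces.

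**Step 2. Smallest significant correlation.** In the Discussion, the relationships in question are between OCTA parameters and systemic markers, so this is the figure most directly on point.
- r = t/√(n − 2 + t²), with n = 1000 and t = 1.962 on 998 degrees of freedom.
- r = 1.962/√(998 + 3.85) = 0.062, so r² = 0.0038, or 0.4% of variance.
- A correlation of 0.089 (0.8% of variance) would already have 80% power.

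**Step 3. Smallest significant group difference and the AUC it implies.** In SD units d = 1.96 × √(1/n₁ + 1/n₂). With normal distributions of equal variance, AUC = Φ(d/√2).

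| Comparison | n₁, n₂ | d | AUC |
|---|---|---|---|
| Retinopathy v none, 10% affected | 100, 900 | 0.207 | 0.558 |
| 20% affected | 200, 800 | 0.155 | 0.544 |
| 30% affected | 300, 700 | 0.135 | 0.538 |
| 40% affected | 400, 600 | 0.127 | 0.536 |
| 50% affected | 500, 500 | 0.124 | 0.535 |
| Controls v all diabetic patients | 100, 1000 | 0.206 | 0.558 |

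For controls against only the patients without retinopathy (600–800 at a 20–40% share), d = 1.96 × √(1/100 + 1/600) = 0.212 to 1.96 × √(1/100 + 1/800) = 0.208. The AUC is about 0.56 in both cases.

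**Step 4. Scale.** An AUC of 0.5 is chance. A difference of d = 0.206 gives a sensitivity of about 14% at 90% specificity. From d = √2 × Φ⁻¹(AUC), an AUC of 0.80 needs d = 1.19 and an AUC of 0.90 needs d = 1.81. For retinopathy versus none at 20–40% affected, 1.19 is roughly eight to nine times the difference that suffices for significance (1.19/0.155 = 7.7; 1.19/0.127 = 9.4).

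**Step 5. Statements set against design and data**

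| Statement | What the plan provides |
|---|---|
| Screening tool for early change (Background) | Group tests and regression; no measure of discrimination named |
| Changes may come before progression (Discussion) | Cross-sectional design; no follow-up outcome among the main or secondary measures |
| Reflects kidney changes (Abstract, Discussion) | Albumin excretion and estimated filtration rate collected, and kidney function used as a secondary factor, so an association can be tested |
| Reflects brain changes (Abstract) | No brain measure listed |
| Reflects tissue seen in heart biopsies (Discussion) | No heart measure listed; heart appears only as an example |

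**The case against.** The strongest reply is that the article states no decision rule. The screening, progression and other-organ remarks are conditional, and the Discussion closes by leaving the technology's potential to this and future trials. The study calls itself exploratory, and the objectives listed after the aim (describing groups and assessing associations) do match the analysis. A condensed article may also leave an accuracy analysis to the full protocol.

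Much of this stands. A reader might infer that the plan will declare OCTA fit for screening whenever p<0.05, or that its conclusions are impossible. The documents do not support either reading: the Discussion gives no threshold, so the link to p<0.05 is an inference from Statistical methods, and the wording is tentative throughout. A reader might also infer that brain and heart are formal objectives left unanswered. They are absent from the objectives in the Background, and heart is mentioned once, as tissue reachable only by biopsy. The kidney part can be tested with the markers collected.

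It is also fair that an AUC against existing retinopathy does not test preclinical detection, which is what the aim is about. The comparison of controls with patients who have no retinopathy is closer to that aim.

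Finally, one might want patients who cannot be imaged counted as screening failures. Inclusion and exclusion criteria keeps them out of the study and does not separate OCTA failure from failure of other examinations, so such a count would need data on people who are not enrolled.

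What remains is a mismatch on the face of the article. The stated aim is a screening role, and the stated analysis does not measure one. A fuller analysis plan could close that gap, but it would not give a cross-sectional study follow-up, and it would leave the Abstract's mention of the brain at odds with the data list.

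**Conclusion.** The point holds as a gap between aim and analysis, together with wording that reaches past the design and data. At 1000 patients a correlation of 0.062 (0.4% of variance) is significant. So is a retinopathy-versus-none difference of about 0.13–0.155 SD at a 20–40% share, with an AUC of about 0.54 (0.53–0.56 over 10–50%). Significance at this sample size is therefore compatible with almost no ability to discriminate.

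These figures assume two-sided tests, normal distributions with equal variance, one independent unit per patient and per control eye, and the stated retinopathy shares. Fewer analysable patients would raise the thresholds somewhat: at 500 the critical correlation is 0.088, still under 1% of variance. The figures describe the smallest effect that would count as significant; they do not predict what OCTA will show. The planned comparisons remain valid for the association objectives.

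**What to change.** - **Statistical methods.** For each main outcome, add the AUC with a 95% confidence interval that allows for clustering of eyes within patients. Do this for (a) controls versus type 1 diabetes without retinopathy, as the measure of early change, and (b) no retinopathy versus retinopathy, as the measure of existing disease. Comparison (b) is already listed in Main outcome measures; (a) is the listed control comparison restricted to eyes without retinopathy. For (b), also report the gain in AUC over age, duration and HbA1c.
- **Basis for screening statements.** Say that any such statement will rest on these estimates and their intervals, not on p<0.05.
- **Abstract and Discussion, other organs.** Limit these claims to the kidney markers collected (albumin excretion and estimated filtration rate), and present brain and heart as hypotheses for future work.
- **Discussion, progression.** State that showing changes come before progression needs follow-up, because this design is cross-sectional.

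The cost is a small extra analysis on data already being collected, and more modest claims. No further recruitment or examinations are needed.
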